## Assignment of interventions: blinding

### Who will be blinded? {17a}

The physicians responsible for assessing the neurologic outcome as well as the neuroradiologist analyzing the brain imaging will be unaware of the treatment-arm. The immediate care-providers, including the attending physician and their team, cannot be blinded during the intervention phase, due to logistical and treatment effects related to xenon-administration.

### Procedure for unblinding if needed {17b}

The need for unblinding should not arise, as the immediate care-providers are not blinded. Only the neuroradiologist and neurologist who assess the primary and/or secondary outcomes are blinded.

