#### Objectives

The primary objective is:

To explore whether xenon is neuroprotective in aSAH patients.

The secondary objectives are to explore the neuroprotective effects of xenon on:

The white matter injury in the cerebellum and corpus callosum. Recent studies have revealed that fractional anisotropy of white matter at 72 h post-SAH measured globally, in the cerebellum and in the corpus callosum, had an independent predictive value for both DCI and for a poor neurological outcome (i.e., mRS 3-6) [44].The incidence and severity of EBI within 72 h after the appearance of SAH symptoms, DCI, and cerebral infarction (according to a consensus statement [17] and consensus guidelines [5]: (1) DCI is defined as a new focal neurological deficit (such as hemiparesis, aphasia, apraxia, hemianopia, or neglect) or a decrease of at least 2 points in the Glasgow Coma Scale (either in the total score or in one of its individual components). This should last for at least 1 h and not be due to other causes (e.g., hydrocephalus, seizures, metabolic derangement, infection, sedation). DCI is not apparent immediately after aneurysm occlusion and cannot be attributed to other causes by means of clinical assessment, CT or MRI scanning of the brain, and appropriate laboratory studies; (2) cerebral infarction is defined as a new infarct on follow-up imaging (i.e., in any of the following: 2nd MRI, CT, CTA, DSA, and perfusion CT) between day 4 and 6 weeks after the initial appearance of SAH symptoms.The incidence of adverse events, serious adverse events, suspected unexpected serious adverse reactionsThe inflammatory process, i.e., assessed by the extent of microglial activation and the levels of cytokine in cerebral spinal fluid (CSF)The need and duration of intracerebral pressure (ICP) treatmentsPlasma catecholamine levelsThe release of troponin TThe release of neuron-specific enolase (NSE), neurofilament light (NF-L), glial fibrillary acidic protein (GFAP), calcium-binding protein S100B (S100B), ubiquitin carboxyterminal hydrolase L1 (UCH-L1), total tau, and cytokines (tumor necrosis factor alpha, interleukins 6 and 10)

The exploratory objectives are:

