### Secondary outcome measures

Fractional anisotropy of white matter at cerebellum and/or at corpus callosum as assessed with the 1st MRI.Safety and tolerability of xenon, as assessed with a ratio of adverse events, serious adverse events, and suspected unexpected serious adverse reactions (SUSARSs) during the follow-up at 1 year between the xenon group and the control group.Composite of radiological EBI (within 72 h after the start of SAH symptoms), DCI, cerebral infarction (see definitions in detail under the section of secondary objectives) and poor outcome (good: mRS 0–2; poor: mRS 3–6) at 3-months and at 1 year.Neurogenic stress cardiomyopathy and stunned myocardium (i.e., myocardial injury caused by sympathetic storm and autonomic dysregulation with hs-troponin elevation, left ventricular dysfunction or ECG changes)ICP-level up to 14 days (i.e., as long as clinically relevant) after the onset of aSAH symptomsNeed for ICP therapies up to 14 days (i.e., as long as clinically relevant) after the onset of aSAH symptomsDuration of therapy for ICP control/monitoring up to 14 days (i.e., as long as clinically relevant) after the onset of aSAH symptomsPlasma catecholamine levelsDifference in selected biomarkers (NSE, NF-L, GFAB, S100B, UCH-L1, total-tau TNF-α, interleukins 6 and 10) and difference in metabolomic and lipidomic profiles in the blood and CSF between xenon and control group in predicting risk for EBI, vasospasm, DCI as well as a good neurological outcome at 3 months, 1 year, and at 2 years after the aSAH.Development of prognostication models with a selected combination of brain imaging and biomarkers obtained from various MRI techniques (see details under the section “Data collection and management”), clinical data, and metabolomics (see details under the section “Data collection and management”) by applying artificial intelligence and machine learning for EBI, vasospasm, DCI, and a good neurological outcome at 3 months, 1 year, and at 2 years after the aSAH.Difference in CTA, DSA, and MRI parameters obtained from various MRI techniques (see details under the section “Data collection and management”) between xenon and control group in predicting EBI, vasospasm, DCI, and a good neurological outcome at 3 months, 1 year, and at 2 years after the aSAH.Predictive value of computational fluid dynamics (CFD) (see details under the section “Data collection and management”) to detect the differences in the blood flow behavior in the recruited patients by applying 3D DSA to assess the risk of EBI within the first 72 h after the start of aSAH symptoms, vasospasm (within 21 days after the start of SAH symptoms) and DCI (between day 4 and 6 weeks after the start of SAH symptoms) and a good neurological outcome at 3 months, at 1 year, and at 2 years after the aSAH (mRS 0–2).Difference of metabolomics and lipidomics profiles of plasma and CSF between xenon and control group and in predicting the risk for EBI within the first 72 h after the start of aSAH symptoms, vasospasm (within 21 days after the start of SAH symptoms) and DCI (between day 4 and 6 weeks after the start of SAH symptoms) and a good neurological outcome at 3 months, at 1 year, and at 2 years after the aSAH (mRS 0-2).Difference of activity of microglial cells between the subjects in the xenon and control groups and in predicting the risk for DCI and a good neurological outcome at 3 months, 1 year, and at 2 years after the aSAH.

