The following MRI techniques will be used: (1) T2-weighted and fluid-attenuated inversion recovery (FLAIR) sequences; (2) T1-weighted 3D gradient echo sequence for volumetric analysis; (3) time of flight angiography (TOF) to visualize flow within vessels, without the need to administer a contrast agent; (4) brain perfusion imaging with dynamic susceptibility contrast (DSC), (5) a susceptibility-weighted imaging (SWI) sequence to image hemosiderin, (6) whole-brain (and region-of-interest level) white matter integrity from diffusion-weighted MRI data measured with diffusion tensor imaging (DTI; fractional anisotropy is the primary end-point of the current trial; (7) voxel-wise white matter microstructure from diffusion-weighted MRI data. A global voxel-wise data-driven Tract Based Spatial Statistics (TBSS) with DTI and other microstructural metrics will be applied; (8) constrained spherical deconvolution (CSD) technique will be used to estimate the orientation of multiple fiber populations, e.g., crossing fibers, in a voxel accurately and within a clinically feasible scan time. The fiber orientation distributions will be estimated with CSD and used to perform probabilistic fiber tractography for the whole brain and for certain tracts of interest. The whole brain tract networks will be analyzed with graph theoretical analysis [49–53].

In addition, all feasible patients (i.e., capable to co-operate adequately during the scan) will be scanned in the Turku PET Centre. The 1st scan will be performed 4 ±1 weeks after the onset of SAH symptoms with the 2nd scan being undertaken at 3 months after the onset of SAH symptoms. It will be explored whether [^11^C](R)-PK11195 can be used to test the hypothesis that xenon can exert a neuroprotective effect and to explore the role of inflammatory process in the extent of DCI and also the neurological outcome at 1 year after SAH. We postulate that this can be demonstrated by showing less signs of microglial activation in the xenon-treated group than in the reference therapy group and in the patients with good outcome, i.e., mRS 0–2 [54–56].

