### Data management {19}

Data collected upon arrival and all neuroradiology findings will be stored in an electronic web-based study database (Redcap, https://www.project-redcap.org/ [62, 63]). This data will be securely stored at the servers of the corresponding city’s universities where the patients are being treated. Intensive care data, including blood pressure, blood samples, and ICP data for example will be stored at a secure server at the corresponding University Hospitals in accordance with hospital guidelines and the Data Management Plan as described below in this protocol.

Access to clinical data with patient IDs is strictly limited to the clinicians treating the patients and maintaining the database. Exports of the clinical data for analyses are always pseudononymized to protect patient confidentiality. The imaging data exports are stored only at MRI unit and Turku PET Centre of Turku University Hospital, which are audited workspace environments that is designed to host sensitive data for collaboration. All researchers sign a non-confidentiality agreement with strict rules on data handling before they are granted access to the exports. The study sites have ethical review board approvals for collection and working with clinical material and data.

All data with direct or indirect identification information will be stored in encrypted form and a separately stored decryption code will be stored with access by the PI. Essential documents shall be archived safely and securely.

Each study patient is identified by a patient code (i.e., first two initials of first and last name and subject number). The patient identity (initials and screening/subject number, the subject’s first name, last name, date of birth, social security number) is recorded on a separate register (i.e., patient identity file) which can be accessed only by the PI with a password. Study subject records, subject screening log, all original signed informed consent forms, and CRFs will be kept in the Investigator’s study file to enable the follow-up assessments by safety committee and monitor. Investigator’s study file can be accessed only by the PI and biostatistician with a password.

The study subject code (initials and screening/subject number), date of informed consent, date of entry or date of exclusion, and the reason for exclusion for those recruited for screening but not fulfilling the inclusion criteria and therefore excluded will be recorded in the subject screening log.

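### The rule that only the neuroradiologist and neurologist are blinded leaves cardiac readers and the biostatistician outside the blind, and does not assure masking for DCI attribution or PET

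*Protocol article*

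**What the plan says.** Two sections of the protocol article deal with masking.

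- Who will be blinded? {17a} names the masked roles: "The physicians responsible for assessing the neurologic outcome as well as the neuroradiologist analyzing the brain imaging will be unaware of the treatment-arm". It continues: "The immediate care-providers, including the attending physician and their team, cannot be blinded during the intervention phase", and gives the logistics and effects of xenon as the reason.
- Procedure for unblinding if needed {17b}: "Only the neuroradiologist and neurologist who assess the primary and/or secondary outcomes are blinded".

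Other sections define outcomes or roles that the two named blinded roles may not cover.

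- Secondary outcome measures lists "Neurogenic stress cardiomyopathy and stunned myocardium", identified by raised hs-troponin, left ventricular dysfunction or ECG changes. No assessor is named.
- Objectives gives the DCI definition: "DCI is defined as a new focal neurological deficit (such as hemiparesis, aphasia, apraxia, hemianopia, or neglect) or a decrease of at least 2 points" on the Glasgow Coma Scale. The event must also be one that "cannot be attributed to other causes by means of clinical assessment", imaging or laboratory work. DCI is a component of a secondary composite. No assessor is named.
- Plans for assessment and collection of outcomes {18a} gives the PET expectation: "We postulate that this can be demonstrated by showing less signs of microglial activation in the xenon-treated group". The scans are done at the Turku PET Centre, and no reader is named.
- Data management {19}, on the investigator's file: "study file can be accessed only by the PI and biostatistician with a password". That file holds subject records and CRFs.

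**The concern.** The trial is open at the bedside, and the article states in advance which direction it expects for cardioprotection, inflammation and DCI. An outcome that needs a reader's judgement can drift in the expected direction if the reader knows the arm. Examples are grading ventricular function, calling an ECG abnormal, quantifying PET uptake, and deciding that a deficit is DCI rather than sedation, seizure or hydrocephalus.

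The word that opens the {17b} sentence makes this more than missing detail. It states a rule on who is masked, and a later document that masked anyone else would contradict it. The reason given in {17a} for open care concerns the intervention phase, which lasts 24 h. It does not explain why recordings read afterwards, or events that arise days later, should be judged with the arm known.

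For the biostatistician the question is discretion. Statistical methods {20a} makes the adjusted analysis the main one and names age, sex and site, but lets other baseline characteristics enter as the need arises. That choice is best made without knowledge of the arms, and it applies to the primary outcome too.

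**Working it through.** The plan gives no figure on this point, so the first step sets the sections side by side.

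| Outcome or role | Assessor stated? | Position under {17a} and {17b} |
|---|---|---|
| Global fractional anisotropy (primary) and MRI secondaries | Neuroradiologist | Masked |
| Neurologic outcome (mRS) | Physicians assessing the neurologic outcome; neurologist | Masked |
| Left ventricular dysfunction, ECG change | No | Not work of either named role as normally understood; outside the blind on a literal reading |
| Biostatistician | Yes, with study-file access | Outside the blind on a literal reading |
| DCI attribution | No | Masked if the blinded neurologist does it; otherwise not |
| PET quantification | No | Masked if it counts as the neuroradiologist's brain imaging; otherwise not |

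Two details bear on the uncertain rows. The steering committee section {5d} lists Cardiology and the Turku PET Centre separately from Neuroradiology, so other staff could well do those reads. Section {26b} has GCS and neurologic condition recorded daily in hospital, without saying by whom.

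Timing: xenon runs for 24 h (Intervention description {11a}). DCI presents at 3–14 days (Background {6a}). PET is at 4 ± 1 weeks and at 3 months ({18a}). DCI and PET therefore fall after the period for which {17a} says masking is impossible. ECG and echo recordings may be made during that period but can be read later.

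The second step is an illustration of size. It uses two document figures, DCI in about 30% of patients (Background {6a}) and 80 per group (Sample size {14}). The assumptions are mine: no true effect, all 80 per arm assessed, and DCI under-called in the xenon arm by a relative fraction f.

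- p1 = 0.30; p2 = 0.30 × (1 − f); d = p1 − p2; p̄ = (p1 + p2)/2
- se0 = √[2 p̄(1 − p̄)/80]; se1 = √[p1(1 − p1)/80 + p2(1 − p2)/80]
- Chance of p<0.05 = Φ[(d − 1.96 se0)/se1] + Φ[(−d − 1.96 se0)/se1]

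For f = 0.20: p2 = 0.24, d = 0.06, p̄ = 0.27, se0 = 0.0702, se1 = 0.0700. The two terms are Φ(−1.108) = 0.134 and Φ(−2.82) = 0.002, which sum to 0.136.

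| f | p2 | Apparent odds ratio | Chance of p<0.05 |
|---|---|---|---|
| 0 | 0.30 | 1.00 | 5% |
| 0.10 | 0.27 | 0.86 | 7% |
| 0.20 | 0.24 | 0.74 | 14% |
| 0.30 | 0.21 | 0.62 | 26% |

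The values of f are not estimates. The table shows only how sensitive a comparison of this size is to modest misclassification in one arm.

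**The case against.** The strongest reply has five parts.

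1. The {17b} sentence explains why emergency unblinding is not needed. The section that defines who is blinded is {17a}, which contains no restriction. This is fair on context, but the sentence is still a plain statement of who is masked, and nothing in the article widens it.

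2. A reader might infer that PET and DCI judgements are unmasked. The documents do not say so. {17a} masks the reader of brain imaging without limiting it to MRI, and PET of microglial activation is brain imaging. DCI is a neurological judgement within a secondary outcome, and {17b} covers the neurologist who assesses secondary outcomes. This part stands: the gap is an unnamed assessor, not a stated unmasked one.

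3. Analyst masking is commonly set in the statistical analysis plan, which is not at hand. {19} also has data exports for analysis pseudonymized and keeps the identity file to the principal investigator. This weakens the analyst limb but does not remove it. Pseudonymization hides who the patient is, not which arm the patient is in. Xenon duration is among the recorded data ({18a}), so the records probably show the arm, though that is an inference. The {17b} wording, taken literally, still excludes the analyst.

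4. It is tempting to size the cardiac bias from the 35% of patients with raised troponin I cited in the Discussion. That does not work. Troponin is an assay result that a reader cannot shift. Only the ventricular-function and ECG elements depend on judgement, and the documents do not give a size for bias in reading them.

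5. This is a phase II trial, and the outcomes whose reading is affected are secondary. This stands and limits the importance of the point.

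**Conclusion.** The point holds in a limited form. As written, {17b} puts the readers of left ventricular dysfunction and ECG change, and the biostatistician, outside the blind. It leaves masking of DCI attribution and PET quantification unassured because their assessors are not named. It should not be read as showing that the primary endpoint is read unmasked: the fractional anisotropy reading and the mRS assessment both have blinded assessors.

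The size of any bias is unknown. The 7% to 26% range rests entirely on the assumed under-calling, a true DCI rate of 30% in both arms and 80 assessed per arm. It applies to DCI only, and only if DCI is in fact judged with the arm known. The conclusion is a worthwhile, inexpensive improvement to the secondary outcomes and to the choice of covariates, not a threat to the trial's main measurement.

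**What to change.** Amend {17a} and {17b} together so that they name the assessors and state their masking:

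- ECG, echo and PET data are read off-line under study number, without the arm.
- DCI attribution, for outcome classification, is confirmed by the already blinded neurologist from records with xenon entries removed.
- The biostatistician works with masked arm labels until models and covariates are fixed, and has no access before then to study-file content that shows the arm.
- The restrictive wording in {17b} is replaced by a reference to this list.

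The cost is labelling and some chart preparation by existing staff; removing xenon entries from ICU records at three sites takes real work, and the documents give no figure for it. No extra patients are needed, bedside care stays open, and treatment is unchanged. Trial status gives recruitment as still to begin, so on the article's own timetable the change could be made before outcome data exist.

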## Data collection and management

### Plans for assessment and collection of outcomes {18a}

Upon hospital arrival and thereafter, basic patient information will be recorded in an electronic web-based study database (RedCap). The data collected on aSAH patients is intended to be both quantitative and qualitative in nature, as recommended by the recent recommendations issued by the working group on subjects’ characteristics, including all relevant Common Data Elements (CDE) [47, 48]. The data to be collected will include details of the patient’s age, sex, home medications and health status, time of insult, hospital arrival delay, vital signs, and blood tests. First computed tomography (CT), computed tomography angiography (CTA), and digital subtraction angiography (DSA) results will be registered in the web-based study’s database according to CDE specifications. During the ICU stay, surgical interventions, vital signs, changes in clinical status, and other medical treatments received will be recorded. The duration of xenon administration will be recorded. In addition, arterial blood gas samples will be monitored hourly during the xenon-treatment phase, and then at least every 4 h or whenever clinically indicated during the ICU stay. The results of the MRI scans at 72 ± 24 h and 42 ± 4 days after the onset of SAH symptoms will be collected in detail according to the CDE recommendations.

The following MRI techniques will be used: (1) T2-weighted and fluid-attenuated inversion recovery (FLAIR) sequences; (2) T1-weighted 3D gradient echo sequence for volumetric analysis; (3) time of flight angiography (TOF) to visualize flow within vessels, without the need to administer a contrast agent; (4) brain perfusion imaging with dynamic susceptibility contrast (DSC), (5) a susceptibility-weighted imaging (SWI) sequence to image hemosiderin, (6) whole-brain (and region-of-interest level) white matter integrity from diffusion-weighted MRI data measured with diffusion tensor imaging (DTI; fractional anisotropy is the primary end-point of the current trial; (7) voxel-wise white matter microstructure from diffusion-weighted MRI data. A global voxel-wise data-driven Tract Based Spatial Statistics (TBSS) with DTI and other microstructural metrics will be applied; (8) constrained spherical deconvolution (CSD) technique will be used to estimate the orientation of multiple fiber populations, e.g., crossing fibers, in a voxel accurately and within a clinically feasible scan time. The fiber orientation distributions will be estimated with CSD and used to perform probabilistic fiber tractography for the whole brain and for certain tracts of interest. The whole brain tract networks will be analyzed with graph theoretical analysis [49–53].

In addition, all feasible patients (i.e., capable to co-operate adequately during the scan) will be scanned in the Turku PET Centre. The 1st scan will be performed 4 ±1 weeks after the onset of SAH symptoms with the 2nd scan being undertaken at 3 months after the onset of SAH symptoms. It will be explored whether [^11^C](R)-PK11195 can be used to test the hypothesis that xenon can exert a neuroprotective effect and to explore the role of inflammatory process in the extent of DCI and also the neurological outcome at 1 year after SAH. We postulate that this can be demonstrated by showing less signs of microglial activation in the xenon-treated group than in the reference therapy group and in the patients with good outcome, i.e., mRS 0–2 [54–56].

Metabolomics will be applied to identify pathophysiological pathways after SAH governing survival, to identify differences in targeted metabolomic pathways between the two treatment groups and discover new biological biomarkers or specific pathways for prognostic purposes. We intend to perform both (i) comprehensive metabolomics analyses using two methods with a broad analytical coverage, for molecular lipids (lipidomics) and polar metabolites, respectively, and (ii) selected targeted/quantitative methods for functionally important metabolites of CNS origin. Among the latter, the proposed methods will include N-acyl amides (NAAs, a class of molecules that encompasses the endocannabinoids and related molecules) and ceramides [57–61].

Human blood vessels will be investigated using computational fluid dynamics (CFD) to detect the differences in blood flow behavior in the recruited patients. CFD will be applied in the dynamic 3D DSA imaging data of the current population with the aim being to investigate and create models of blood flow behavior in the proximity of the ruptured aneurysms, and in distant regions as well as globally. Artificial intelligence (AI) and machine learning (ML) will be used by combining the results of CFD simulations and clinical data to create models which possess a high predictive accuracy for estimating the risk for EBI, vasospasm, and DCI and poor neurological outcome in aSAH patients. The predictive accuracy of the prognostication models created in derivation cohorts of the retrospective population will be tested in retrospective validation cohorts and in individual cases, and in the prospective Xe-SAH population. The retrospective population (initially collected by JK and IS) will comprise all consecutive aneurysm cases which will have been detected in the catchment area of the Hospital District of Southwest Finland from January 2000 to May 2018 (i.e., Turku Aneurysm Data, TAD). Altogether, over 2600 unique aneurysm patients have been recorded into TAD. In all cases, the automatic text mining will be performed by Auria Biobank Service (Turku, Finland) registering all the clinical, radiological, laboratory, and other available events throughout the history of each individual patient before and after the diagnosis of the aneurysm. The total amount of events in the TAD constitutes over 70,000,000.

